### Statistical analysis

All analysis will be prespecified and conducted according to the intention-to-treat principle with the use of SPSS version 20 (IBM, Armonk, NY, USA). Each incision will be randomized to the NPWT or standard dressing group. In the case that a patient requires bilateral incisions, the right side will be randomized and the left side will be automatically placed in the opposite arm but not be included in the primary analysis as there is a loss of independence. Baseline characteristics of the two groups will be recorded. The continuous variables will be compared using Student’s *t* test. The categorical variables will be compared using Pearson’s chi-square or Fisher’s exact test depending on the number of events. The proportion of SSIs amongst randomized groins will be compared between the NPWT and standard dressing groups using a chi-square test or Fisher’s exact tests depending on the number of events. An absolute risk increase/reduction for SSI will be presented for the use of NPWT, as well as the number needed to treat to prevent a single SSI. Patients lost to follow-up have the outcome last assessed treated as his or her final outcome. A secondary analysis will be performed including the nonrandomized groin in patients with bilateral incisions. We will also perform a subgroup analysis on just patients undergoing bilateral incision using McNemar’s test.

Secondary outcomes will be compared between groups using a chi-square test for categorical variables. Non-normally distributed continuous variables will be compared using the Mann–Whitney *U* test. A *p* value of less than 0.05 will be considered significant and all tests will be two-sided.

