### Sample size

Our previous study revealed a SSI rate of 22 % in all patients requiring femoral artery exposure for vascular surgical procedure at LHSC [4]. This study will only include high-risk patients as defined above and we expect the wound infection rate to be higher. Matatov et al. demonstrated a reduction of groin SSI with NPWT from 30 % to 6 %, an absolute risk reduction of 24 % and relative risk reduction of 80 % [6]. Given an alpha of 0.05, for 80 % power, this yields a required sample size of 48 patients per group using the Fleiss method with continuity correction. The planned sample size will account for potential loss of follow-up, device malfunction and patient incompliance and has been adjusted to a final sample size of 54 (10 % increase from calculated sample size) groin incisions per group and a total study sample of 108 groin incisions. The timeline for recruitment is 20 months and with a 90-day follow-up the study will be concluded in 2 years.

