## Discussion

This trial is the first randomized controlled trial to investigate the role of NPWT in reducing the incidence of SSIs following surgery for lower limb revascularization in high-risk patients. Matatov et al. retrospectively reviewed 115 groin incisions in 90 patients who received either NPWT or adhesive gauze dressing following vascular procedure [6]. The authors demonstrated a reduction of SSI from 30 % to 6 % and no grade II or III infections in the NPWT cohort [6]. Our hypothesis is that high-risk patients in this study will see a similar benefit of reduction of SSIs.

Draining fluid following lower limb revascularization is not a new concept and in the past surgical drains placed deep in the wound have been investigated with randomized trials and meta-analyses, which did not show a reduced rate of SSI [17–19]. Significant research has been invested into the mechanism of action of NPWT on wound healing leading to four primary effects: macrodeformation; stabilization of the wound environment; reduced edema and microdeformation [17]. In conjunction with reticulated open-cell foam, such as used in the current study, NPWT can have a stimulatory effect on cellular proliferation and angiogenesis. Further, by actively removing excessive interstitial fluid and edema, it is thought secondary necrosis is reduced [18]. On a molecular level, cytokine and growth factor expression are modulated to an anti-inflammatory profile and culminate in angiogenesis, remodeling and granulation tissue [19]. The closed suction environment placed under sterile conditions also effectively separates the incision from the surrounding environment theoretically preventing the inoculation of environmental bacteria.

This trial will clarify the role of NPWT and its potential for reduction in SSI in groin incisions for lower limb revascularization. The major limitation of this trial is the inability to blind the surgical team and the patient. We will randomize the incisions once the incision is primary closed to reduce the bias that could occur from the surgical team.

The results of this trial will be used to determine the role of NPWT in the prevention of SSI. If this intervention is shown to be effective for the prevention of SSI in this high-risk population, significant benefit with respect to both patient morbidity and resource utilization may be achieved.

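### The sample size is derived in patients but the target is set in groin incisions, and the protocol does not say whether left groins excluded from the primary analysis count toward the 108

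*Protocol article*

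**What the plan says.** The Sample size section of the protocol article takes its effect from a cited retrospective cohort, a "reduction of groin SSI with NPWT from 30 % to 6 %, an absolute risk reduction of 24" percentage points, and states that "this yields a required sample size of 48 patients per group using the Fleiss method with continuity correction". It then raises 48 to 54 for loss to follow-up, device malfunction and non-compliance. In doing so it changes the unit: the 54 are groin incisions per group, and the target is "a total study sample of 108 groin incisions".

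Under Randomization and again under Statistical analysis, a bilateral patient has the right groin randomized and the left groin put automatically in the other arm. That left groin is "placed in the opposite arm but not be included in the primary analysis as there is a loss of independence". It returns later: "A secondary analysis will be performed including the nonrandomized groin in patients with bilateral incisions". A McNemar analysis of the bilateral patients is also planned.

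The wording on what counts toward 108 is not consistent. The abstract speaks of 108 incisions being randomized. The Statistical analysis section calls the left groin nonrandomized, yet also says that each incision is randomized. The Sample size section speaks only of the total study sample. No expected share of bilateral patients is given.

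**The concern.** The calculation needs independent units, and the primary analysis uses one groin per patient to secure independence. A target counted in incisions matches that analysis only if every counted incision is an index groin. If left groins also fill the 108, recruitment stops with fewer primary units than planned. The increase from 48 to 54 is assigned to other causes, so nothing is reserved for this.

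The share of bilateral patients is unlikely to be negligible. The first example operation under Eligibility is a femoral-to-femoral crossover bypass, and the plan provides a separate analysis for bilateral patients. At stake are the point at which recruitment stops and whether the stated power describes the analysis that will be run.

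**Working it through.** **Inputs from the protocol.** "Given an alpha of 0.05, for 80 % power"; "all tests will be two-sided"; 30% v 6%, so d = 0.24 and mean rate 0.18; 48 required and 54 planned per group; 108 in total. **Assumption:** the bilateral share s. The only hint is the cited cohort, which "retrospectively reviewed 115 groin incisions in 90 patients". If each of the 25 extra incisions is a second groin, s = 25/90 = 27.8%.

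**1. Reproducing the 48.**
- Uncorrected n = [1.96·√(2·0.18·0.82) + 0.842·√(0.21 + 0.0564)]² / 0.24² = 39.03.
- Continuity correction: (n/4)·[1 + √(1 + 4/(n·d))]² = 46.99, that is 47. Rounding 39.03 up to 40 first gives 47.97, that is 48.
- The stated 48 therefore stands, and 48/0.9 = 53.3 rounds up to the stated 54.

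**2. Primary units if 108 counts every groin.** With B bilateral patients there are 108 − B patients, each giving one primary unit. Assuming an even split, that is (108 − B)/2 per arm. This is at least 48 only while B ≤ 12. At B = 12 there are 96 patients (12.5% bilateral), and the whole margin over 96 has been used. In terms of the share, units per arm = 54/(1 + s).

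**3. Power by the protocol's own method.** Inverting the correction gives an effective uncorrected size m = (n − 1/d)²/n. Power is Φ{[d·√m − 1.96·√(2·0.18·0.82)] / √0.2664}. At s = 27.8%, n = 42.26 and m = 34.34, so power = 0.746.

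| Assumed share bilateral | Patients | Primary units per arm | Power, corrected formula |
|---|---|---|---|
| 0% | 108.0 | 54.0 | 86% |
| 10% | 98.2 | 49.1 | 82% |
| 12.5% | 96.0 | 48.0 | 81% |
| 15% | 93.9 | 47.0 | 80% |
| 20% | 90.0 | 45.0 | 78% |
| 27.8% | 84.5 | 42.3 | 75% |

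No losses are deducted here (see the objection).

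**4. Exact power at 42 per arm, 30% v 6%.** Enumerating both binomials gives 86% for Pearson's chi-square and 80% (79.5%) for Fisher's test. Using chi-square but switching to Fisher when an expected count is below 5 (an assumed rule; the article says only that the choice depends on the number of events) gives 86%.

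**5. If 108 counts index groins only.** There are 108 patients and 54 primary units per arm, with no shortfall. At the assumed mix the trial would then dress 108 × 115/90 = 138 groins.

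**6. What the left groins would add.** At the assumed mix of 84.5 patients, 108 − 84.5 = 23.5 are bilateral. The standard errors of the risk difference are:
- Index groins only: √(0.2664/42.3) = 0.079.
- All 108 incisions: √{[0.2664·54 − 2ρ·√(0.21·0.0564)·23.5]/54²}, which is 0.070 at within-patient correlation ρ = 0 and 0.068 at ρ = 0.2.

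The covariance term lowers the variance because paired groins sit in opposite arms.

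**The case against.** The strongest reply is that 108 already means index groins. The abstract has 108 incisions randomized, the Statistical analysis section calls the left groin nonrandomized, and the primary comparison is of randomized groins. In that vocabulary nothing is missing. This reading is permitted but not secured: the same section says each incision is randomized, and the Sample size section counts the total study sample. The point is therefore an ambiguity with a conditional consequence.

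The bilateral share is also borrowed. The cited cohort is retrospective, is not described as this trial's high-risk population, and its extra incisions are not said to be second groins. That stands, which is why a range is shown.

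Four stronger readings are tempting, and the protocol does not support them:
- **A further 10% loss leaves 38 per arm and 69% power.** The plan is intention-to-treat and carries forward the last assessed outcome, so patients lost to follow-up stay in the analysis. Device malfunction and non-compliance remove no one either.
- **80% power is not delivered.** This holds only if left groins count, the share is high enough, and the corrected formula is the yardstick. Exact power at 42 per arm is 86% with chi-square, and only just under 80% if Fisher's test is used throughout.
- **The within-patient data are set aside.** The McNemar analysis and the secondary analysis both use them.
- **The secondary analysis is defective because no method is named.** A condensed article may leave that to the full plan.

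Finally, one groin per patient is a valid primary analysis. A clustered analysis is a gain in precision, not the correction of an error.

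**Conclusion.** The point holds in conditional form. The change of unit, the exclusion of left groins and the lack of any allowance for them are all in the text. Whether they cause a shortfall depends on a counting rule that the protocol does not state.

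If all groins count, the primary analysis drops below the plan's own 48 per group with more than 12 bilateral patients and no losses. By the protocol's formula, power goes from 82% at 10% bilateral to 78% at 20% and about 75% at 28%. The shortfall against 48 does not depend on the test; whether power drops below 80% does. These figures rest on 30% v 6%, an even split of index groins between arms, and an assumed bilateral share.

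**What to change.** In the Sample size section, do one of the following:

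1. State that the 54 per group are independent randomized index groins, one per patient, and that left groins are additional. If the all-groin count was intended until now, this means recruiting 108 patients rather than about 84.5 at the assumed mix. If index groins were always meant, it costs one sentence.
2. If 108 counts all groins, give the expected number of independent groins per arm and the matching power over a range of bilateral shares, as in the table. This needs no extra patients but states a less favourable power.

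The abstract and the Statistical analysis section should then use the same unit and the same meaning of randomized.

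Preferably, also make the main analysis one of all incisions with the patient as cluster (GEE or a cluster-robust risk difference with 95% CI), keeping the right-groin-only chi-square as a sensitivity analysis. The left groin's arm is the complement of a random draw, so including it is valid, and modelling the pairing answers the protocol's stated reason for leaving it out. The cost is a slightly more complex model and no added patients. Because the trial is open-label and Trial status reports 46 patients enrolled, the change should be dated and made without sight of outcomes by arm.

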### Intervention and control

The intervention group will have NPWT, the Prevena Incision Management System (Kinetic Concepts Inc, San Antonio, TX, USA), applied to the primary closed groin incision. The Prevena system has a silver interface with a foam layer connected to a small portable battery-operated vacuum unit. The vacuum is preset to continuous at 125 mmHg. The device is applied under sterile conditions in the operating room and remains on the patient until the hospital discharge or postoperative day 8, whichever occurs first. The wound will be inspected for any evidence of infection once the Prevena is removed. The device is used only once and is disposed of at the end of the study. Any concern about the wound or the device will require removal of the NPWT earlier than planned and will be recorded as a secondary endpoint of the trial.

The control group will have a standard sterile gauge dressing to cover the groin incision. The postoperative management is typically removal of the dressing on day 2 postoperatively with daily dressing changes thereafter. All other pre- and postoperative care of patients will be the same in both groups. Hair will be removed with electric clippers preoperatively. Skin preparation will be done with 2 % chlorhexidiene. Every patient will received preoperative antibiotics (cephalexin or vancomycin if penicillin allergy is present) and postoperative antibiotics will be given for 48 h. At the end of the operation, the groin incision will be primary closed with either skin staples, monocryl or prolene sutures.

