### Definition of primary endpoint and outcome measures

The primary endpoint is the incidence of superficial SSI within 30 days of surgery. SSI is defined by the Center for Disease Control and Prevention (CDC) criteria [15] as: infection occurring within the first 30 postoperative days involving skin and subcutaneous tissue of the incision and at least one of the following:Purulent drainage from the incisionOrganisms isolated from an aseptically obtained culture of fluid or tissue from the incisionAt least one of the following signs/symptoms of infectionPain or tendernessLocalized swellingRednessHeatOR incision is deliberately opened by a surgeon (unless incision is culture negative)4.Diagnosis of SSI by the surgeon or attending physician

Once the SSI is identified, the Szilagyi classification of vascular wound infections will be used to classify to infection [16]. This classification categorizes vascular SSI based on dermal involvement (I), subcutaneous involvement (II) or arterial graft involvement (III).

SSI will be assessed daily, at discharge, and reassessed at the outpatient clinic within 30 days following the operation.

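### Carrying the last assessed outcome forward counts patients lost after an infection-free discharge as observed 30-day non-infections, so the rule can only understate SSI

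*Protocol article*

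**What the plan says.** The protocol article gives one rule for missing primary outcomes, under Statistical analysis: "Patients lost to follow-up have the outcome last assessed treated as his or her final outcome". It names no sensitivity analysis for these patients.

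Under Definition of primary endpoint and outcome measures, the endpoint is fixed as follows: "The primary endpoint is the incidence of superficial SSI within 30 days of surgery". The schedule is: "SSI will be assessed daily, at discharge, and reassessed at the outpatient clinic within 30 days following the operation". No other SSI assessment is scheduled between discharge and day 30.

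Under Intervention and control, the NPWT device "remains on the patient until the hospital discharge or postoperative day 8, whichever occurs first". The protocol thus expects some patients to go home by about day 8, with some three weeks of the endpoint window still to run.

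The Sample size section expects some loss: "The planned sample size will account for potential loss of follow-up". The same 10% allowance also covers device malfunction and non-compliance.

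**The concern.** Every groin starts as SSI-free, and a recorded SSI stays recorded. Carrying the last status forward can therefore change the result in one way only: an unknown later status becomes no SSI. For a patient lost straight after discharge, the rule assumes zero risk over the rest of the 30 days.

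Three consequences follow.

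- Recorded SSI rates are too low in any arm with such losses.
- The imputed values enter the chi-square or Fisher test, the absolute risk reduction and the number needed to treat as if observed, with no allowance for their uncertainty.
- If loss differs by arm, which is possible in a trial where patients and clinical staff are unblinded, the rule itself can shift the comparison.

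Because the plan states this rule, it is not a detail left to a separate analysis plan.

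**Working it through.** **1. The plan's own figure.** Inputs from Sample size: the cited study "demonstrated a reduction of groin SSI with NPWT from 30 % to 6" per cent; "Given an alpha of 0.05, for 80 % power, this yields a required sample size of 48 patients per group". The formula named there is that of Fleiss, corrected for continuity. Tests are two-sided (Statistical analysis).

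- Uncorrected: n′ = [1.96·√(2·0.18·0.82) + 0.8416·√(0.30·0.70 + 0.06·0.94)]² / 0.24² = 39.03, rounded up to 40.
- Corrected: n = (n′/4)·[1 + √(1 + 4/(n′·0.24))]². This gives 46.99 (47) from n′ = 39.03, and 47.97 (48) from n′ = 40.
- Inflation: 48/0.9 = 53.3, rounded up to 54.

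The stated 48 and 54 are reproduced. The sample size is not at issue here.

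**2. Bias formula.** Let p be the true 30-day SSI risk in an arm, d the share lost, and s the share of SSIs that arise after last contact. With loss unrelated to infection, the recorded rate is p·(1 − d·s). The documents do not give s, or d by arm, so both are assumptions.

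**3. Balanced loss.** Take d = 10% in each arm. This is a ceiling, since the allowance also covers two other causes.

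| s | Control | NPWT | Difference |
|---|---|---|---|
| 0 (truth) | 30.0% | 6.0% | 24.0 points |
| 50% | 28.5% | 5.7% | 22.8 points |
| 70% | 27.9% | 5.6% | 22.3 points |

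The relative fall is 5–7%. The difference shrinks by 1.2–1.7 points, towards no effect. Over a wider range of s, 25–75%, the difference is 23.4–22.2 points. Power at 54 per arm without continuity correction goes from 91.2% to 90.3–88.3%, and with correction from 86.2% to 84.9–82.1%.

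**4. Unequal loss.** The recorded difference is (pC − pN) − s·(pC·dC − pN·dN), where C is control and N is NPWT.

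- With no true effect (30% in both arms), the spurious benefit is 0.30·s·(dN − dC). For assumed losses of 5% control and 15% NPWT, this is 1.5 points at s = 50% and 2.25 points at s = 75%. For an assumed 5% and 20% with s = 60%, it is 0.30·0.60·0.15 = 2.7 points. Reversing the losses reverses the sign.
- At 30% and 6%, the risk difference is inflated only if 0.06·dN exceeds 0.30·dC, that is, if NPWT loss is more than five times control loss. The risk ratio is multiplied by (1 − dN·s)/(1 − dC·s), so it always moves in favour of the arm with more loss.

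**5. Stress test.** The planning rates give 0.30·54 ≈ 16 and 0.06·54 ≈ 3 events. Ten per cent of 54 is about 5 groins per arm. The rule reports the first row whatever happened to the lost groins.

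| Control vs NPWT (of 54) | Unseen infections assumed | Fisher p | Pearson p |
|---|---|---|---|
| 16 vs 3 | none | 0.0018 | 0.0010 |
| 16 vs 6 | 3 NPWT | 0.030 | 0.017 |
| 16 vs 7 | 4 NPWT | 0.059 | 0.034 |
| 16 vs 8 | 5 NPWT | 0.104 | 0.064 |
| 17 vs 8 | 5 NPWT, 1 control | 0.067 | 0.040 |
| 21 vs 8 | 5 in each arm | 0.009 | 0.005 |

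**The case against.** **The result is robust at the planning rates.** A reader might infer from the 16 vs 8 row that a handful of losses would probably decide the trial. The documents do not support that. The row needs all 5 lost NPWT groins infected and no lost control groin infected. At an independent 30% risk, 5 of 5 has probability 0.30⁵ = 0.0024, and at 6% it is below one in a million. Under Pearson's test, significance survives 4 of 5, and one infected control groin restores it. This stands: the row is a stress test, not a forecast.

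**The loss is overstated.** The 10% allowance is shared, and under intention-to-treat, groins with device malfunction or non-compliance can stay in follow-up. This stands: 5 lost per arm is a ceiling. Nor does anything in the documents indicate a 5% versus 20% split or a 60% post-contact share.

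**The bias is conservative.** Under balanced loss the difference shrinks, which works against a superiority claim. This stands for balanced loss and a real effect. It does not protect the comparison under unequal loss, and the absolute SSI rates and the number needed to treat remain wrong.

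**Missing the clinic is not always loss.** Emergency visits, surgery for SSI and deep SSI to 90 days are collected, and a surgeon's or attending physician's diagnosis meets the SSI definition. This stands in part: such contact can supply a later status, but it does not help a patient with no contact after discharge.

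**A day-30 completeness rule would misfire.** A tempting remedy is to call every SSI-free patient last seen before day 30 incomplete. The clinic visit is scheduled within 30 days, not on day 30, so that remedy would censor or impute patients who had followed the schedule. A rich within-arm imputation model would also be unstable with about 3 expected NPWT events. Both points stand and shape the fix.

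**The covered NPWT wound.** The first direct inspection may come only at device removal. That is a question of ascertainment, separate from this missing-data rule.

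**Conclusion.** The concern holds. As stated, the rule turns an unknown status after discharge into an observed non-infection. It can only understate SSI, treats imputed values as data, and can tilt the comparison if loss differs by arm.

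The expected size is modest under balanced loss: 5–7% relative on each rate, and 24 points reduced to 22.8–22.3, assuming 10% lost per arm and 50–70% of infections after last contact. With no true effect and the unequal losses assumed above, the spurious benefit is about 1.5 to 2.7 points. The move from p = 0.0018 to p = 0.10 is an extreme corner only.

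The direction of the error in recorded SSI follows from the plan's own text. Its size depends on loss by arm and on the timing of infections, neither of which the documents give. The rule still needs replacing: it is the only stated handling of missing primary outcomes, and no sensitivity analysis is named that would reveal its effect.

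**What to change.** - Stop using the last outcome carried forward as the primary handling; keep it as a sensitivity analysis.
- Define complete follow-up as a recorded SSI, attendance at the planned post-discharge clinic assessment, or another documented SSI status after discharge. Recorded SSIs remain events.
- Treat SSI-free patients with no assessment after discharge as missing.
- In the primary analysis, either censor them at last assessment and compare 30-day SSI risk, or use multiple imputation with a simple model that the small event count can support. If censoring is chosen, say how deaths before day 30 are handled.
- Add a best/worst-case or tipping-point table by arm for the lost groins, and report loss by arm.

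The cost is about a paragraph of wording, a slightly wider interval and a little more analysis work. The article describes 46 patients enrolled against 108 planned incisions, so at that stage the change could still be fixed before analysis.

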### Randomization, allocation concealment and blinding

Once the groin incision is primary closed, randomization will be done using internet-based software, sealedenvelope.com (London, UK), via random permutated blocks. If the patient has bilateral groin incisions, the right groin will be randomized and the left groin will be automatically placed in the other arm. The surgical team, clinical staff, and patient will not be blinded to the intervention status. The primary outcome of SSI will be assessed by a clinical specialist nurse who will be blinded to the intervention status.

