### Secondary endpoints

Secondary endpoints include length of stay, emergency room visits, SSI requiring surgical intervention, deep SSI occurring within 90 days of an operation, limb amputation, and mortality. A cost analysis will also be performed using the average cost provided by LHSC for inpatients, return visits, and any surgical intervention. Outcomes related to potential harm will also be identified including local reaction to the NPWT device, and the need for early removal of the dressing.

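### Patients with bilateral incisions receive both dressings, so including them in between-group comparisons of length of stay, emergency visits, mortality and cost dilutes any effect

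*Protocol article*

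**What the plan says.** The allocation rule is in Randomization, allocation concealment and blinding: "If the patient has bilateral groin incisions, the right groin will be randomized and the left groin will be automatically placed in the other arm". This rule is repeated in the Statistical analysis section, which adds that the left groin will "but not be included in the primary analysis as there is a loss of independence". Two further analyses use the second groin: one adds the nonrandomized groins, the other applies McNemar's test in the bilateral subgroup.

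The Secondary endpoints section opens its list with "Secondary endpoints include length of stay, emergency room visits" and goes on to SSI needing surgery, deep SSI, amputation and mortality. On cost it states: "A cost analysis will also be performed using the average cost provided by LHSC for inpatients, return visits, and any surgical intervention".

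For the analysis of secondary outcomes, the article gives two sentences on tests. One is "Secondary outcomes will be compared between groups using a chi-square test for categorical variables" and the other, for continuous data, is "Non-normally distributed continuous variables will be compared using the Mann–Whitney *U* test". Neither says how a patient with an incision on each side is handled.

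**The concern.** Some of the secondary endpoints belong to a groin or limb, such as deep SSI, SSI needing surgery and amputation. Others belong to the patient: there is one length of stay, one count of emergency visits, one vital status, and one inpatient and return-visit cost. A bilateral patient has one NPWT groin and one gauze groin whichever way the right side is randomized. For a patient-level outcome, the arm label of that patient therefore does not distinguish NPWT from gauze.

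The article recognizes the bilateral problem where it sets out the primary analysis, but does not carry it over to these outcomes. The two planned bilateral analyses do not help, because an outcome that is identical for both of a patient's groins gives no within-patient contrast.

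The Discussion looks forward to benefits in patient morbidity and resource use. Resource use rests largely on these patient-level outcomes, and a diluted difference in stay or cost could be misread as absence of benefit.

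**Working it through.** **The plan's own figure.** For SSI of 30% against 6%, two-sided alpha 0.05 and 80% power, the continuity-corrected formula gives 47 per group. The Sample size section states 48, so the figure reproduces closely. Allowing for 10% loss, 48/(1 − 0.10) = 53.3, rounded up to 54 per group. This calculation concerns SSI and is untouched by the present point.

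**Inputs**
- Allocation of the two groins: Randomization, allocation concealment and blinding.
- Patient-level outcomes: Secondary endpoints.
- 54 per arm: Sample size. It is used here as an illustrative number of randomized patients per arm; the article states it as groin incisions.
- b, the share of randomized patients who are bilateral: not given for this trial, so assumed at 10%, 20% and 30%.
- Assumption: a bilateral patient's expected patient-level outcome is the same whichever side carries NPWT.

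**Right-groin label.** Let Δ be the NPWT-minus-gauze difference in unilateral patients. Bilateral patients contribute an expected difference of zero, so the overall expected difference is (1 − b)Δ + b × 0 = (1 − b)Δ.

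**Both groins entered.** With N patients, each arm holds N(1 − b)/2 unilateral records and Nb bilateral records. The unilateral share is [(1 − b)/2] / [(1 − b)/2 + b] = (1 − b)/(1 + b), and the expected difference shrinks by that factor. The same stay, visit, death or cost also appears in both arms, which breaks the independence that chi-square and Mann–Whitney assume.

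**Power.** Take the standardized effect that has 80% power with 54 per arm at b = 0: d = (1.960 + 0.842) × √(2/54) = 0.539.
- Right-groin label: power = Φ[2.802(1 − b) − 1.960]. At b = 20%: Φ(2.241 − 1.960) = 61%.
- Unilateral patients only, 54(1 − b) per arm: power = Φ[2.802√(1 − b) − 1.960]. At b = 20%: Φ(2.506 − 1.960) = 71%.

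| Assumed b | Effect retained, right-groin label | Effect retained, both groins entered | Power, right-groin label | Power, unilateral only |
|---|---|---|---|---|
| 10% | 90% | 82% | 71% | 76% |
| 20% | 80% | 67% | 61% | 71% |
| 30% | 70% | 54% | 50% | 65% |

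Since √(1 − b) exceeds (1 − b) for every b between 0 and 1, leaving bilateral patients out gives more power than keeping them under the right-groin label. This assumes a common variance and does not depend on the choice of 54.

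**The case against.** The strongest reply is that the article does not say that bilateral patients enter these comparisons, and that a condensed article may leave such a rule to a fuller document. That is fair as to which records are used. However, the article itself states both the opposite-arm allocation and the between-group comparison, and under either way of including these patients the difference is diluted. Intention-to-treat supplies a label for the patient but not a treatment contrast.

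Several stronger readings are tempting but not supported:

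- A reader might infer that bilateral patients make the comparison invalid. Under the right-groin label it is still a randomized comparison and valid under the null. The fault is dilution, not excess false positives.
- A reader might infer that the same patient will be counted in both arms. The Statistical analysis section keeps the left groin out of the primary analysis and brings it back in a separately named one. This suggests that randomized groins are the default, so double counting is only a possibility.
- A reader might take b from the retrospective cohort in the Discussion: 115 incisions in 90 patients, so 25/90 = 28% if nobody had more than two. Nothing shows that this share carries over to the present high-risk population.
- A reader might infer that cost is biased towards NPWT because the device is not among the listed components. The article does not say whether the average inpatient cost includes it, so no direction of bias is established.
- A reader might ask for cluster models for groin-level outcomes. Analysing randomized groins alone gives one record per patient, and no error is shown there.

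It also stands that the trial is powered only for SSI, and that at a low bilateral share the gain is modest: 71% to 76% at b = 10%.

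**Conclusion.** The point holds for patient-level secondary outcomes and for the inpatient and return-visit parts of cost. With bilateral patients included under the right-groin label, the expected difference is (1 − b) of the unilateral effect: 90%, 80% and 70% at assumed shares of 10%, 20% and 30%. Were both groins entered, the factor would be (1 − b)/(1 + b), with independence lost as well.

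The size depends on b, which the article does not give for this trial, and on the assumption that the side carrying NPWT does not matter for these outcomes. If bilateral cases are rare, the dilution is small. Some are to be expected, since femoral-to-femoral crossover is named as an example operation under Eligibility and two bilateral analyses are planned. The primary SSI analysis and the sample size are unaffected.

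**What to change.** State in the Statistical analysis section that length of stay, emergency room visits, mortality and cost are compared between arms in patients with a single groin incision, and that patients with bilateral incisions are described separately. Keep groin-level outcomes on the randomized groins, with the planned bilateral analyses as supplements. At most, add a sentence on whether the cost of the device is counted.

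This changes the wording of the analysis and not the conduct of the trial. Bilateral status is known before randomization, so the restricted comparison is still a randomized one. The price is fewer patients in these comparisons, and results that apply to unilateral operations only. Even so, power is higher than with bilateral patients kept in, for example about 65% against 50% at b = 30%.
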